**Fig. 1 Fig1:**
[figure not shown]
The standardized, high flow nasal cannula weaning pathway including eligibility criteria (light orange box), weaning criteria (dark orange boxes), the point of deployment of the REST EEC randomized workflow (light blue box), specific management guidance (dark blue boxes), ongoing management guidance (green boxes), and the work of breathing score used to guide objective patient assessments (table below the algorithm)

### Randomization

The intervention is the provision of clinical decision support to guide bedside nurses and respiratory therapists in the systematic weaning of HFNC for children with bronchiolitis. The control is usual care, which consists of a clinical pathway for HFNC weaning without associated clinical decision support. Ordering clinicians are the target of randomization, but the unit of randomization is a clinician-patient decision moment. Accordingly, each time a clinician has decided to initiate HFNC for a patient eligible for REST EEC, randomization will occur in an unblinded, automated, and 1:1 ratio between the intervention and usual care arms. Only the CDS intervention is randomized and all other components of care are not specified by the study design, instead proceeding according to usual care. As the intervention involves CDS to reinforce an existing standard of care and the endpoint is duration of HFNC, a respiratory support modality that is the focus of de-implementation campaigns and not considered an established standard of care, the University of Pittsburgh Institutional Review Board approved waiver of consent for the REST EEC trial. Randomization is automated and cued by placement of a “HFNC for Bronchiolitis” Cerner PowerPlan (orderset) and based on whether a specific digit in the encounter identifier, which is a Cerner Millennium database key not readily apparent to clinicians and specific to a patient hospital encounter, is even or odd. Encounter identifiers are assigned sequentially as patients are registered for an interaction with the healthcare system, ensuring that the assignments are equally and randomly distributed between the 2 trial arms.

### Current clinical operations prior to study initiation

Figure 1 is the HFNC weaning clinical effectiveness guideline available to clinicians at CHP at the time of REST EEC initiation. HFNC is provided from children < 2 years old using the either the Fisher & Paykel Optiflow circuit or the Airvo 2 heated high flow device with an Airvo circuit and Optiflow junior cannulas (all manufactured by Fisher & Paykel Healthcare, Auckland, New Zealand) and initiated at 1–2 mL/kg of flow per clinician discretion and as indicated in the clinical effectiveness guideline. HFNC management is overseen by board-certified or eligible pediatric intensivists and duration is determined on an individual basis according to patient response and the need for escalation versus weaning. Following development of the guideline, an education session was held with all respiratory therapists detailing the guideline contents and responding to questions. Pediatric clinical effectiveness guidelines are available for all UPMC clinicians on the health system’s intranet and the HFNC weaning guideline was first made available in the winter of 2022–2023. A laminated copy of the guideline is also placed on the HFNC equipment and therefore available in hard copy at the bedside of each patient receiving HFNC. The guideline is revisited at least annually by a committee of intensivists, respiratory therapists, nurses, and informaticians with updates made as needed during those annual reviews. Prior to REST EEC, HFNC was initiated after placement of an “Oxygen Therapy” Cerner PowerPlan in which clinicians could select between 2 options: (1) “Do Not Wean Oxygen Without Physician Order/Modification” (*sic*); (2) “RT/RN may wean O2, following the weaning order” (*sic*). The choice of HFNC as the delivery device (as opposed to, for example, a Venturi mask) was specified within the “Oxygen Therapy” PowerPlan. Among the patients receiving HFNC for bronchiolitis in the PICU whose data were used for trial simulations, none received an order for standardized weaning prior to the deployment of the REST EEC study.

### Study intervention and associated workflow

A new electronic workflow was developed to deploy the REST EEC trial. Clinicians, including pediatric intensivists, pediatric intensive care fellows, pediatric emergency medicine physicians, general pediatrics residents, emergency medicine residents, emergency and intensive care nurse practitioners, and emergency and intensive care physician assistants, are responsible for diagnosing bronchiolitis in children. The intervention arm consists of clinical decision support that includes an order bearing instructions for the HFNC weaning process, as outlined in the guidelines, that is placed in the “Respiratory Care” section of the Cerner orders. This order is also linked to a scheduled task that appears on both the nursing and respiratory therapy tasks lists, requesting that a WOB score be documented every 2 h and the ability to wean HFNC assessed by either of those clinicians caring for the patient. This intervention differs from the usual care arm, in which the HFNC weaning guideline is accessible to the clinical team via the UPMC intranet, but decisions to wean HFNC are made ad hoc by the clinical team. By requiring every 2-h assessments, the investigators hypothesize that the duration of HFNC will be shorter among patients randomized to the intervention arm of REST EEC, as compared to the usual care arm. The REST EEC design does not include any guidance on therapies outside the use of HFNC. The decision to discontinue or modify HFNC is left to the bedside clinician responsible for patient care; the CDS serves as a guide.

To accommodate the unique patient population of interest, the clinical effectiveness guideline workflow, and the need for randomization, a “HFNC for Bronchiolitis” PowerPlan was constructed leveraging features of Cerner’s PowerFlex PowerPlan technology. PowerFlex PowerPlans allow for dynamic PowerPlan characteristics according to programmed rules that can draw upon individual patient characteristics. To ensure that patients > 2 years of age are not randomized, the “HFNC for Bronchiolitis” PowerFlex PowerPlan cannot be ordered for patients 2 years or older. If attempting to place the PowerPlan, clinicians receive a message stating that the patient is not eligible for the order and asking them to remove the PowerPlan. For patients < 2 years old, the REST EEC trial eligibility criteria are displayed at the top of the PowerPlan and clinicians are instructed to sign the PowerPlan only if patients meet the criteria (Fig. 2). The REST EEC study arms, one for the intervention and one for usual care, are both available as options within the PowerPlan, alongside instructions to clinicians stating “The pre-selected orders below are based on randomization and should only be changed if the physician/APP thinks it is in the best interest of the patient.” The randomized assignment is pre-selected using the PowerFlex feature when the PowerPlan is opened but can be changed if a clinician has a strong preference. The intervention group are those patients for whom CDS is ordered and the control group are those patients who receive usual care without CDS. A new WOB score documentation field was also built in a segment of the electronic flowsheet that overlaps with nursing and respiratory therapist workflows, allowing both disciplines to document the score as requested by the HFNC weaning guideline. REST EEC is deployed as part of usual care and all ancillary and post-trial care occur according to usual care.

**Fig. 2 Fig2:**
[figure not shown]
Screenshot of the Cerner “Bronchiolitis HFNC Oxygen Therapy PowerPlan.” Eligibility criteria are listed at the top of the PowerPlan, with instructions to clinicians to remove the PowerPlan if the patient does not meet criteria. The green box outlines the section of the PowerPlan that is pre-selected according to the patient’s randomized assignment

### Endpoints

The primary outcome is duration of HFNC measured from the time of initiation of the HFNC PowerPlan to final weaning off of HFNC support evidenced by documentation of nasal cannula flow less than 4 L per minute among patients who do not require noninvasive or invasive ventilation following randomization, up to 30 days. The design is open label with only outcome assessors being blinded so unblinding will not occur. For patients requiring noninvasive or invasive ventilation following randomization, the duration of HFNC will be measured following last documented mode of positive pressure ventilation preceding placement on HFNC. Secondary outcomes include respiratory support free days, organ support free days, PICU length of stay, hospital length of stay, time to oral intake, respiratory distress measured by the WOB score, geographically adjusted cost of care for hospitalization, and mortality. Data to calculate the endpoints will be collected from the EHR and the PHIS database. Follow-up is limited to the hospitalization during which the patient received HFNC and long-term follow-up beyond hospitalization is not planned for the REST EEC trial.

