### Statistical model, simulation results, and statistical analysis plan

The primary endpoint analysis will be conducted according to each patient’s randomized assignment. To provide an estimate of the effect of the intervention on the primary outcome of duration of HFNC, we use a semiparametric Bayesian proportional hazards regression model. This model has two components. The baseline hazard component models the underlying chance of weaning off of HFNC over time for standard of care. The hazard ratio (HR) component models the CDS intervention effect as the proportional change in the chance of weaning for those randomized to CDS. Because the exact form of the baseline hazard is unknown, we specify a flexible model which can accommodate a wide range of possibilities. Specifically, the baseline hazard is modeled using cubic M-splines with two boundaries and two internal knots at equally spaced percentiles of the distribution of uncensored HFNC durations with a flat Dirichlet prior distribution over the spline coefficients. A weakly informative N(0, 2.5) prior is used for the intervention log(HR) parameter. This prior is centered at a HR of 1 implying no difference between standard of care and CDS and has a negligible impact on the posterior treatment effect estimate. The model is implemented using the stan_surv() function in the rstanarm modeling package [21].

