As REST EEC uses an adaptive Bayesian design, virtual trial simulations were conducted to understand statistical design operating characteristics such as sample size, trial duration, and power for putative trial scenarios with a given intervention effect size and to determine feasibility of the planned design. To inform the Bayesian analysis plan, data were extracted from the CHP EDW staged environment, which contained all CHP encounters for the preceding 3 years. Supplemental Table 1 displays the data dictionary used to define the preliminary data to inform simulations. There were 549 encounters that received HFNC with a primary or secondary diagnosis of bronchiolitis. The estimated median time to weaning was 35 h (Fig. 3). Several trial scenarios were explored, with varied accrual rates and effect sizes as measured by the difference in median time to weaning between the CDS intervention arm versus usual care. For each scenario, 5000 virtual trials were simulated and the behavior of each trial was tracked to determine the design operating characteristics. An anticipated effect evidenced by a HR of 1.27, or a 6-h difference between the median time to weaning in the CDS versus usual care arm, was selected as providing a clinically significant but realistic effect of the intervention. HFNC weaning in the CHP PICU commonly occurs following PICU morning rounds. A 6-h decrease in HFNC duration therefore commonly translates into a morning rather than afternoon discharge out of the PICU, which can subsequently facilitate earlier hospital discharge. Three interim analyses (at 12 months, 18 months, and 24 months after study initiation) and one final analysis (at the maximum sample size) will be performed. At each interim analysis, the study will declare superiority of CDS if the posterior probability of HR > 1 exceeds 0.99 or futility of CDS if the posterior probability of HR < 1.15 exceeds 0.8, meaning that futility will be declared if the probability is > 0.8 that the effect of clinical decision support is less than a 4-h reduction in HFNC duration. If neither condition is met, the study will continue to the next interim or final analysis. At the final analysis, CDS will be declared superior if the posterior probability of HR > 1 exceeds 0.9. A clinically actionable posterior probability threshold at which the CDS would be considered “statistically promising” and left in place following trial conclusion was determined to be 0.8 after conferring among the investigators and clinical leadership. Planning for balanced randomization between the CDS intervention and usual care, with a maximum sample size of 350 over approximately 2–3 years (100–150 patients per year), trial simulations indicate there will be a > 0.75 probability of declaring superiority (either interim analysis posterior probability of HR > 1 greater than 0.99 or final analysis posterior probability of HR > 1 greater than 0.9) and a > 0.85 probability of declaring superiority or the CDS intervention showing promise (final analysis posterior probability of HR > 1 greater than 0.8) (Fig. 4). This design was deemed feasible as approximately 150 children with bronchiolitis < 2 years old receive HFNC annually at the study site. Planned secondary analyses include evaluating the primary endpoint among select subgroups, including children treated with beta agonists therapy, children treated for pneumonia, children with complex chronic conditions, children receiving positive pressure ventilation, and children co-diagnosed with croup. The electronic data collection strategy has been designed to encode missing data as absent, avoiding the need for imputation. The primary analysis will be intention to treat (ITT) and a secondary, modified ITT analysis will be performed based on assignments that may have been altered by the ordering clinicians.

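### The primary-outcome clock restarts after post-randomisation ventilation, so extra ventilation under CDS would be diluted in the hazard ratio and could even read as benefit

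*Protocol article*

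**What the plan says.** The Endpoints section sets two clocks for one primary outcome.

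- Children not ventilated after randomisation: "duration of HFNC measured from the time of initiation of the HFNC PowerPlan to final weaning off of HFNC support". Weaning is shown by a documented flow below 4 L/min, and follow-up runs to 30 days.
- Children who receive noninvasive or invasive ventilation after randomisation: "For patients requiring noninvasive or invasive ventilation following randomization, the duration of HFNC will be measured following last documented mode of positive pressure ventilation".

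The statistical section keeps all children in their allocated arm: "The primary endpoint analysis will be conducted according to each patient’s randomized assignment". It labels this intention to treat. The model reads a higher weaning rate as benefit: "The hazard ratio (HR) component models the CDS intervention effect as the proportional change in the chance of weaning for those randomized to CDS". Interim superiority, interim futility, final superiority and the 'promising' category are all defined on the posterior for this one HR.

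The secondary outcomes include respiratory support free days, organ support free days and mortality. A subgroup of children receiving positive pressure ventilation (PPV) is planned, analysed on the same primary endpoint. The section on data collection says that there is no data monitoring committee.

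**The concern.** Randomisation makes the arms comparable at order placement. For ventilated children the outcome starts later, at a point fixed by their course after randomisation. The CDS prompts a weaning assessment every 2 h, so it could plausibly change who is ventilated. If it does, the two arms hold different proportions of children on the restarted clock. Analysing children by allocated arm does not repair that.

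The restart also discards the hours that would show the harm. Take a child with 24 h of HFNC, 72 h of noninvasive ventilation and a final 10 h of HFNC. Time from randomisation to final weaning is 24 + 72 + 10 = 106 h. The recorded outcome is 10 h, well under the 35-h baseline median.

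At stake is the trial's conclusion. The final thresholds are low (posterior probability above 0.9 for superiority, above 0.8 for promising), so a modest upward shift in the HR matters.

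**Working it through.** **Inputs from the article.** Baseline median 35 h; HR 1.27 corresponding to 6.08 h (Fig. 3 legend); maximum 350 children, 1:1; interim rules P(HR > 1) > 0.99 for superiority and P(HR < 1.15) > 0.8 for futility; final thresholds 0.9 and 0.8; 30-day limit; "A weakly informative N(0, 2.5) prior is used for the intervention log(HR) parameter", which the article calls negligible in effect.

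**Assumed inputs (not in the documents).** PPV rates by arm; HFNC before PPV with median 12 h; PPV with median 48 h; HFNC after PPV with median 8 to 50 h (all exponential); 35 h taken as the median for children not ventilated; CDS has no effect on those children.

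**1. The plan's own power figure.** For the final look alone, with 350 events and a flat prior, z = √350 × ln(1.27) / 2 = 18.71 × 0.239 / 2 = 2.24.
- P(superior) = Φ(2.24 − 1.28) = 0.83.
- P(superior or promising) = Φ(2.24 − 0.84) = 0.92.
- With the interim rules, at 100, 125 and 150 children a year: 0.774, 0.789 and 0.801 for superiority; 0.831, 0.848 and 0.865 for superiority or promising.

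These agree with the stated > 0.75 and > 0.85 to within about 2 points. The power claim is not in question here.

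**2. Shape of the weaning curve.** A Weibull curve consistent with the plan has shape ln(1.27) / ln(35 / (35 − 6.08)) = 0.239 / 0.191 = 1.25.

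**3. Two scorings of the same children.** Let X be the weaning time of a child not ventilated. For a ventilated child let A be HFNC before PPV, B the PPV time and C the HFNC after PPV.
- As written: X, or C if ventilated.
- From randomisation: X, or A + B + C if ventilated.

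Cox HR for CDS against usual care, 200,000 simulated children per arm, capped at 30 × 24 = 720 h, PPV 10% usual care versus 20% CDS:

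| Median HFNC after PPV | HR as written | HR from randomisation |
|---|---|---|
| 8 h | 1.09 | 0.89 |
| 15 h | 1.06–1.07 | 0.88 |
| 24 h | 1.02–1.03 | 0.86 |
| 28–30 h | about 1.00 | 0.85–0.86 |
| 35 h | 0.98 | 0.85 |
| 50 h | 0.94 | 0.84 |

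Ranges reflect repeat runs. At 10% versus 15% the HR as written is about 1.04, 1.03 and 1.01–1.02 at 8, 15 and 24 h, and 0.99 at 35 h; from randomisation it is 0.92–0.94. With 10% in both arms both HRs are 1.00 apart from simulation noise.

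**4. Effect on the decision.** A second model used exponential weaning times with mean 12 h before PPV and mean 48 h of PPV. It applied the stated interim and final rules at 10% versus 20% PPV:

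| Median HFNC after PPV | P(superior) as written | P(superior) from randomisation |
|---|---|---|
| 12 h | 0.25 | 0.04 |
| 18 h | 0.20 | 0.03 |
| 24 h | 0.16 | 0.02 |
| 35 h | 0.10 | 0.01 |

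With equal PPV rates P(superior) is about 0.09 to 0.10 under either clock. In this model the HR as written is 0.97 at 50 h and 0.93 at 70 h, against 0.88 and 0.86 from randomisation.

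**The case against.** The case on the other side has several parts, and much of it stands.

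- **The bias needs unequal ventilation.** Correct. The documents give no rates. Both arms have the same weaning guideline, the bedside clinician keeps the decision, and the article calls the intervention minimal risk. Nothing in it says that over-rapid weaning is a main risk, so a doubling of PPV is an illustration, not a forecast.
- **Reversal is not general.** A reader might infer that this rule always turns harm into benefit. The documents do not support that. It depends on post-PPV HFNC being shorter than about 28–30 h under the first model (35 h under the second), and that duration is not given. Above it, harm is weakened but keeps its sign.
- **Not every failed wean is affected.** A reader might infer that any child who fails weaning is scored short. A child who returns only to HFNC is timed from order placement to final weaning and so scores long. PPV can also reflect disease progression.
- **Other outcomes may reveal harm.** Respiratory and organ support free days, mortality and the PPV subgroup may do so. None enters the decision rule, and the subgroup inherits the restarted clock.
- **Edge cases.** How a ventilated child who never returns to HFNC, or who dies, is scored may be settled in the full plan. No fault is claimed there.
- **The aim is HFNC duration.** A clock that includes ventilation hours measures something broader. This is fair, and the fix offers an alternative.

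What the objection does not remove is that the restart is a stated rule, and its trigger is an event after randomisation.

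**Conclusion.** The point holds in a limited form. The start of the primary outcome depends on an event that the CDS may affect, so the comparison is not fully protected by randomisation. With equal PPV rates there is no bias. In every scenario run with more PPV under CDS, the rule moved the HR towards CDS.

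At an assumed 10% versus 20%, an HR of about 0.84–0.89 from randomisation is recorded as 0.94–0.98 when post-PPV HFNC has a median of 35–50 h, and as 1.02–1.09 when it is 8–24 h. The first is dilution and the second is reversal. The documents do not say which range applies. At 10% versus 15% the shift is smaller.

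This should be fixed rather than being fatal to the design: its size rests on assumed rates and durations, and secondary outcomes may partly show the harm. It matters because every declared conclusion rests on this HR alone.

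**What to change.** - **Primary analysis:** start the clock at first order placement for every randomised child. Define the event as the last documented flow below 4 L/min with no later HFNC, noninvasive or invasive ventilation, up to 30 days. Count PPV time and in-hospital death as not weaned.
- **If an HFNC-only estimand is preferred:** keep the clock at randomisation and treat post-randomisation PPV as a competing (not-weaned) event.
- **Present definition:** keep it as a sensitivity or secondary analysis.
- **Secondary outcome:** report PPV after randomisation by arm, so that the condition for bias can be seen directly.

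Cost: wording in the protocol and analysis plan, one change to the extraction query (the linked intensive care data mart already holds duration of mechanical ventilation), and a re-run of the simulations. The price is a longer right tail from ventilated children and, under the first option, a somewhat broader estimand than HFNC hours.

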### Statistical model, simulation results, and statistical analysis plan

The primary endpoint analysis will be conducted according to each patient’s randomized assignment. To provide an estimate of the effect of the intervention on the primary outcome of duration of HFNC, we use a semiparametric Bayesian proportional hazards regression model. This model has two components. The baseline hazard component models the underlying chance of weaning off of HFNC over time for standard of care. The hazard ratio (HR) component models the CDS intervention effect as the proportional change in the chance of weaning for those randomized to CDS. Because the exact form of the baseline hazard is unknown, we specify a flexible model which can accommodate a wide range of possibilities. Specifically, the baseline hazard is modeled using cubic M-splines with two boundaries and two internal knots at equally spaced percentiles of the distribution of uncensored HFNC durations with a flat Dirichlet prior distribution over the spline coefficients. A weakly informative N(0, 2.5) prior is used for the intervention log(HR) parameter. This prior is centered at a HR of 1 implying no difference between standard of care and CDS and has a negligible impact on the posterior treatment effect estimate. The model is implemented using the stan_surv() function in the rstanarm modeling package [21].

As REST EEC uses an adaptive Bayesian design, virtual trial simulations were conducted to understand statistical design operating characteristics such as sample size, trial duration, and power for putative trial scenarios with a given intervention effect size and to determine feasibility of the planned design. To inform the Bayesian analysis plan, data were extracted from the CHP EDW staged environment, which contained all CHP encounters for the preceding 3 years. Supplemental Table 1 displays the data dictionary used to define the preliminary data to inform simulations. There were 549 encounters that received HFNC with a primary or secondary diagnosis of bronchiolitis. The estimated median time to weaning was 35 h (Fig. 3). Several trial scenarios were explored, with varied accrual rates and effect sizes as measured by the difference in median time to weaning between the CDS intervention arm versus usual care. For each scenario, 5000 virtual trials were simulated and the behavior of each trial was tracked to determine the design operating characteristics. An anticipated effect evidenced by a HR of 1.27, or a 6-h difference between the median time to weaning in the CDS versus usual care arm, was selected as providing a clinically significant but realistic effect of the intervention. HFNC weaning in the CHP PICU commonly occurs following PICU morning rounds. A 6-h decrease in HFNC duration therefore commonly translates into a morning rather than afternoon discharge out of the PICU, which can subsequently facilitate earlier hospital discharge. Three interim analyses (at 12 months, 18 months, and 24 months after study initiation) and one final analysis (at the maximum sample size) will be performed. At each interim analysis, the study will declare superiority of CDS if the posterior probability of HR > 1 exceeds 0.99 or futility of CDS if the posterior probability of HR < 1.15 exceeds 0.8, meaning that futility will be declared if the probability is > 0.8 that the effect of clinical decision support is less than a 4-h reduction in HFNC duration. If neither condition is met, the study will continue to the next interim or final analysis. At the final analysis, CDS will be declared superior if the posterior probability of HR > 1 exceeds 0.9. A clinically actionable posterior probability threshold at which the CDS would be considered “statistically promising” and left in place following trial conclusion was determined to be 0.8 after conferring among the investigators and clinical leadership. Planning for balanced randomization between the CDS intervention and usual care, with a maximum sample size of 350 over approximately 2–3 years (100–150 patients per year), trial simulations indicate there will be a > 0.75 probability of declaring superiority (either interim analysis posterior probability of HR > 1 greater than 0.99 or final analysis posterior probability of HR > 1 greater than 0.9) and a > 0.85 probability of declaring superiority or the CDS intervention showing promise (final analysis posterior probability of HR > 1 greater than 0.8) (Fig. 4). This design was deemed feasible as approximately 150 children with bronchiolitis < 2 years old receive HFNC annually at the study site. Planned secondary analyses include evaluating the primary endpoint among select subgroups, including children treated with beta agonists therapy, children treated for pneumonia, children with complex chronic conditions, children receiving positive pressure ventilation, and children co-diagnosed with croup. The electronic data collection strategy has been designed to encode missing data as absent, avoiding the need for imputation. The primary analysis will be intention to treat (ITT) and a secondary, modified ITT analysis will be performed based on assignments that may have been altered by the ordering clinicians.

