Trial conduct, interim analyses, and final analyses are also relying on observational data sources, including both the EHR and local data submitted to the Pediatric Health Information Systems (PHIS) database, which is a large, multicenter, benchmarking database for children’s hospitals that harbors predominantly administrative data including encounter dates, care-related charges, and diagnosis codes. PHIS offers additional data elements not readily retrievable from the EDW, including geographically adjusted costs of care, complex chronic comorbidities flags as defined by Feudtner et al. [20], and an additional set of risk scores providing predicted mortality (based on administrative admission data) and expected mortality (based on administrative data from the entire encounter) for use as additional balance measures. PHIS is maintained by Children’s Hospital Association (Lenexa, KS) and can be accessed using a web application version of SAP Business Objects (SAP, Walldorf, Germany). PHIS data are deidentified but can be linked to local, single center patient data via a decryption key possessed by designated individuals at the site, as we have previously done for observational studies. A data monitoring committee was not deemed necessary as the intervention is minimal risk.

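### The positive pressure ventilation subgroup has no baseline limit, so its membership and time zero can both follow randomisation and the arm comparison within it is not randomised

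*Protocol article*

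**What the plan says.** The subgroup plan is in the section on the statistical model, simulation results and analysis plan: "Planned secondary analyses include evaluating the primary endpoint among select subgroups". The groups listed are "children treated with beta agonists therapy, children treated for pneumonia, children with complex chronic conditions, children receiving positive pressure ventilation, and children co-diagnosed with croup". Three are named by treatment received, one by comorbidity and one by co-diagnosis. No time window is given for any of them.

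On timing, the Randomization section says that "each time a clinician has decided to initiate HFNC for a patient eligible for REST EEC, randomization will occur", so assignment coincides with the order to start HFNC. The same section adds: "Only the CDS intervention is randomized and all other components of care are not specified by the study design".

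The Endpoints section defines duration from PowerPlan initiation "among patients who do not require noninvasive or invasive ventilation following randomization". For the others it changes the starting point: "For patients requiring noninvasive or invasive ventilation following randomization, the duration of HFNC will be measured following last documented mode of positive pressure ventilation". It also states: "The design is open label with only outcome assessors being blinded".

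**The concern.** A subgroup comparison keeps the protection of randomisation only if membership is settled before assignment, or cannot be changed by it. On the article's own description, ventilation can come after assignment. The intervention prompts a weaning assessment every 2 h, and clinicians know the arm. The pace of weaning could therefore change which children go on to ventilation. If so, the ventilated children in the two arms are different kinds of children.

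The restarted clock adds to this. For a child ventilated after randomisation, HFNC time before ventilation and the time on ventilation drop out, and only HFNC after the last ventilation counts. In this subgroup, then, entry and time zero may both be consequences of the arm.

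The stake is interpretation. The Discussion says CDS stays in place if it proves statistically promising and clinicians find it useful on review of the final analyses. An apparent benefit or harm in ventilated children could colour that review. Ventilation after randomisation is not itself a named secondary outcome; respiratory support free days reflects it only indirectly. A difference between arms in who is ventilated could therefore go unseen while its by-product appears as a subgroup effect.

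**Working it through.** The article gives no figure for this subgroup, so there is nothing of its own to reproduce. The check asks what HR the subgroup would show if CDS had no effect on any child's HFNC time.

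**Inputs from the article:** maximum N 350; 1:1 allocation (175 per arm); planned HR 1.27.

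**Assumed inputs (not in the article):** ventilation in 10% of control and 12% or 15% of CDS children; exponential HFNC times after ventilation; median 24 h for children who would be ventilated in either arm; median 8 to 48 h for the extra children ventilated only under CDS.

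**Step 1: mixture.** The share of extra children among ventilated CDS children is (p_CDS − p_control)/p_CDS.
- 10% v 12%: 0.02/0.12 = 0.167
- 10% v 15%: 0.05/0.15 = 0.333

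**Step 2: Cox HR in the ventilated subgroup** (large simulated samples, so sampling error is negligible):

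| Median in extra children | 10% v 12% | 10% v 15% |
|---|---|---|
| 8 h | 1.12 | 1.27 |
| 12 h | 1.09 | 1.19 |
| 18 h | 1.04 | 1.09 |
| 24 h (same as the rest) | 1.00 | 1.00 |
| 36 h | 0.92 | 0.86 |
| 48 h | 0.87 | 0.77 |

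The true effect is nil in every cell. If the extra children are milder, CDS looks beneficial; if they are sicker, it looks harmful.

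**Step 3: a second mechanism.** A latent severity drives both HFNC duration and ventilation, and CDS changes only the odds of ventilation. Control rate 10% or 20%; severity coefficient on the log hazard 0.5 or 1.0; 1,000,000 patients per scenario; no clock restart.

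| Odds ratio of CDS on ventilation | HR, all randomised | HR, ventilated subgroup |
|---|---|---|
| 0.5 | about 1.00 | 0.92–0.96 |
| 1.0 | about 1.00 | about 1.00 |
| 2.0 | about 1.00 | 1.05–1.10 |

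The whole-trial comparison stays at 1.00 while the subgroup moves in either direction. The distortion disappears when CDS does not alter ventilation.

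**Step 4: precision at N = 350.** SE(log HR) = √(1/d_control + 1/d_CDS), with every child weaned.
- 10% v 12%: 17.5 + 21 = 38.5 children; √(1/17.5 + 1/21) = 0.32
- 10% v 15%: 17.5 + 26.25 = 43.75 children; √(1/17.5 + 1/26.25) = 0.31

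The extremes, log(1.27) = 0.24 and log(0.77) = −0.26, each lie within one SE. Sampling noise would exceed the bias in a single trial, but the bias does not shrink as numbers grow.

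**Step 5: the other four subgroups.**
- Beta agonists, pneumonia treatment: named by treatment, no window. The same mechanism applies only if treatment begun after randomisation is counted.
- Complex chronic conditions: drawn from PHIS "complex chronic comorbidities flags", a comorbidity rather than care given. Not affected.
- Croup: a co-diagnosis. A concern only if coded from the whole encounter.

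**The case against.** The strongest reply is that the article condenses a protocol and analysis plan, version 1.0, that is not shown, and time windows are ordinarily settled there. For beta agonists and pneumonia treatment this largely stands: the article leaves the window open and does not state a post-randomisation definition. For ventilation it stands less well. The published wording describes receipt, not a baseline characteristic, and the Endpoints section itself places ventilation after randomisation.

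Three stronger readings are tempting, and the document does not support them.
- A reader might infer that all five subgroups are formed by care given after randomisation. Two are not care at all, and two others have an unstated window.
- A reader might infer that the bias favours CDS and reaches the full planned effect. An HR of 1.27 needs half as many ventilated children again and a median one third of control's. Equally arbitrary inputs in the other direction give 0.77, and the severity model gives only 0.92–1.10. Nothing in the article says whether the extra children would be milder or sicker, or that there would be any.
- A reader might infer that the trial's main conclusion is at risk from the subgroup plan. The superiority, futility and promising thresholds apply to the primary endpoint, analysed by randomised assignment, and no threshold is attached to a subgroup.

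It is also fair to say that the restarted clock belongs to the primary endpoint and affects the whole-trial analysis too. It is cited here only because it makes time zero, as well as membership, depend on events after assignment in this subgroup.

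**Conclusion.** The point holds for the ventilation subgroup. As worded, it permits a comparison of arms among children selected on an event after randomisation that the intervention could change, with time zero moved by the same event. For beta agonists and pneumonia treatment it holds conditionally, if later treatment is counted.

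Under the assumed inputs and no true effect, the subgroup HR lies between about 0.77 and 1.27. It is 1.00 if CDS leaves the ventilated group unchanged or if the extra children wean like the rest. The range rests wholly on assumed ventilation rates and medians, and shows only that the result could mislead in either direction. With SE(log HR) of about 0.31–0.32 the subgroup would also be imprecise. Because these are secondary analyses and no primary decision rule depends on them, severity is minor to moderate.

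**What to change.** Define the three treatment-based subgroups by EHR time-stamped status at or before the first opening of the PowerPlan: ventilation before it, beta agonist before it, pneumonia treatment before it. Drop ventilation after randomisation as a subgroup and report it by arm, among all randomised children, as an outcome. Complex chronic conditions can stay as it is. For croup, state whether the diagnosis is taken at presentation or from the whole encounter.

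The cost is a sentence or two in the analysis plan, a time-stamp filter on data taken from the EHR, and smaller subgroups. The ventilation subgroup in particular may become too small for more than description.
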